### Study significance

Based on a solid foundation of child mental health studies, this study will answer key questions regarding the effectiveness of school-based psychosocial interventions for improving mental health in rural Chinese children. This study will apply an implementation science approach, and we expect to develop a cultural adaptation of intervention strategies in the Chinese cultural context. The direct translational research-to-policy implications of this work can revolutionize how mental health intervention programs are delivered in rural primary, middle and high schools.

## Methods

### Study design and randomization

As shown in Fig. 1, this study is a multicenter cluster randomized controlled trial. School as the study unit will be randomly assigned to the intervention or the control group. Four rural counties in Shandong (Central China), Henan (Central China), Inner Mongolia (Northern China), and Xinjiang (Western China) will be selected as study settings. These counties were selected due to their vulnerability in socioeconomic development and weakness of the mental health system. In addition, we have good cooperation with the local schools in these areas, which ensure a high participation rate. The schools were randomly allocated to either the intervention or control group using a random number generator. Randomization will be performed by the research member who is not involved in the intervention stage. Grade 5 above in each school will be recruited to ensure that approximately 50 children aged 10 to 18 years are included. After being informed about the survey’s aims, children will be asked to provide informed consent and informed that they can join the study voluntarily. Informed consent also will be obtained from their parents/legally authorized representatives.

**Fig. 1 Fig1:**
[figure not shown]
Flowchart of intervention and control situations in the study design

### Sample sizes and subjects

The required sample size to detect an expected intervention effect with sufficient statistical power was calculated for the primary outcome posttraumatic stress symptoms, as measured with the PTSD Checklist for DSM-5 (PCL-5) scale, using a method that considers the estimation of effect size, repeated measurements, significance level, power, allocation ratio, and attrition rate at T2, and T3. The following parameters are used: (1) the effect size estimations for the primary outcome is 0.20 (based on a meta-analysis [33]); (2) the intraclass correlation is 0.05; 4) 5% level of significance; 5) 80% level of power; 6) allocation ratio of 1:1; and 7) attrition rate of 20%. Under these hypotheses, we expect a sample size of at least 24 clusters (i.e., schools) with 50 children in each school to be included, resulting in a total intended sample size of 1200 children, 1200 parents and 30 teachers. The sample size will be distributed as evenly as possible among the control schools and intervention schools.

Eligibility criteria: As school is our intervention unit, the inclusion criterion is that the school should not have a similar psychosocial intervention program. For students, all children in the program schools who have signed informed consent will participate in this program. Exclusion criteria: Children with severe physical and mental health problem, and unable to participate into the program completely.

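### The listed sample size parameters do not yield 24 schools of 50 children; 80% power at an effect of 0.20 rests on a repeated-measures input that the article does not give

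*Protocol article*

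**What the plan says.** The section Sample sizes and subjects calculates the size for the "primary outcome posttraumatic stress symptoms, as measured with the PTSD Checklist for DSM-5 (PCL-5) scale". It says that the method took account of repeated measurements and of attrition at T2 and T3, among other things. The effect size is 0.20, taken from a meta-analysis. The list continues "2) the intraclass correlation is 0.05; 4) 5% level of significance; 5) 80% level of power", followed by "allocation ratio of 1:1" and 20% attrition. The numbering goes from 2 to 4, so there is no item 3. From these assumptions the section concludes "we expect a sample size of at least 24 clusters (i.e., schools) with 50 children in each school to be included", which makes 1200 children.

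The section Statistical methods plans a three-level mixed model with treatment, time and their interaction, a random intercept and slope for the child, and a random intercept for the school. The effect is to be reported as the difference between arms at T2 and at T3, with 95% confidence intervals. The section Assessments places T1 one week before the intervention.

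**The concern.** The article presents 24 schools of 50 as the consequence of the parameters that it lists. A reader who puts those parameters into the usual cluster-trial formula gets more than twice as many schools. So either the figure is wrong for its inputs, or it depends on an input that was left out and that decides the answer.

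The Background criticises earlier school-based studies for low power, and the strengths section counts the large sample as an asset. If the stated 80% has no basis, readers will give a null result more weight than the design allows.

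**Working it through.** **Inputs from Sample sizes and subjects.** Effect 0.20; intraclass correlation (ICC) 0.05; alpha 5%; power 80%; 1:1 allocation, so 12 schools per arm; 50 children per school; 20% attrition, so 50 × 0.8 = 40 analysed per school.

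**Assumptions, not stated in the article.** The effect is a standardised mean difference (SD = 1), the test is two-sided, the ICC is at school level, and schools are of equal size.

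**1. Trying to reproduce 24 × 50 from the listed inputs**

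- Without clustering: n per arm = 2(1.96 + 0.8416)² / 0.20² = 392.4, so 393.
- Design effect with 40 analysed: 1 + 39 × 0.05 = 2.95.
- Children analysed per arm: 392.4 × 2.95 ≈ 1158. Schools per arm: 1158 / 40 = 28.9, so 29, or 58 in total. With a t correction it is 60.
- With no attrition (50 analysed): design effect 1 + 49 × 0.05 = 3.45; 392.4 × 3.45 ≈ 1354 per arm; 1354 / 50 = 27.1 schools per arm.
- Ignoring clustering: 2 × 393 = 786 children, or 786 / 0.8 ≈ 983 with attrition. Neither is 1200.

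The stated figure is not reproduced.

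**2. Power of 12 against 12 schools with no repeated-measures gain**

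SE = √[(2/12)(0.05 + 0.95/40)] = √[(2/12) × 0.07375] = 0.1109.

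| Setting | Normal | t, 22 df |
|---|---|---|
| Effect 0.20, 40 analysed per school | 43.8% | 40.7% |
| Effect 0.20, 50 analysed (no attrition) | 46.2% | 43.0% |
| Effect 0.20, 40 analysed, one-sided | 56.3% | 54.1% |

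The effect detectable with 80% power is 2.8016 × 0.1109 = 0.31 (normal), or about 0.33 (t).

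Changing a listed input can bring the figure back: an effect of 0.30 without attrition gives 79.9%, and an ICC of about 0.011 without attrition gives 80%. Both contradict what the article states.

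**3. What repeated measurements would have to supply (40 analysed per school)**

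For 80% power at 0.20 the SE must fall to 0.20 / 2.8016 = 0.0714. The variance must then fall to (0.0714 / 0.1109)² ≈ 0.41 of its unadjusted value. Let r be the correlation of school means over time.

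- *One follow-up adjusted for baseline*, variance factor 1 − r². Power (normal) is 55% at r = 0.5 and 71% at r = 0.7. It reaches 80% at r of about 0.77 (t: 0.79).
- *Mean of T2 and T3 adjusted for baseline*, the same r between all time points, factor (1 + r)/2 − r². Power is 72% at r = 0.5. It reaches 80% at about 0.64 (t: 0.68).
- *School effect constant over time*, child-level correlation c: r = (0.05 + 0.02375c) / 0.07375. For c = 0.30, r = 0.775, and the adjusted single time point has 81% power (t: 78%). For c = 0.35, r = 0.791 and power is 84% (t: 80%).
- *Baseline reduces only the within-school variance*: the school part, 0.05, remains. SE cannot fall below √[(2/12) × 0.05] = 0.0913, so power is at most 59% (t: 55%) at any correlation.

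Depending on this unreported input, the same 24 schools have anything from about 44% to 80% or more (normal approximation).

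**The case against.** The strongest case for the plan is that the article does say that repeated measurements entered the calculation, and that the gap at item 3 looks like a dropped parameter rather than a wrong sum. The main gain would come from T1, which is scheduled and which the time term can use. The planned model has a random intercept for school and no school-by-time term, so it takes the school effect as constant over time. Under that assumption a moderate child-level correlation of about 0.30-0.35 is enough for about 80% with a baseline-adjusted contrast.

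This stands. A reader might infer that the trial has 41-44% power, or that it will more likely than not miss its target effect. The article does not support that: those percentages describe an unadjusted comparison at one follow-up, not the power of the planned mixed model. Nor can it be said that 24 × 50 arises only from a larger effect or a smaller ICC, because the repeated-measures routes above also reach it.

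It does not remove the fault. The article lists its parameters and presents the size as following from them, and the ones shown do not give it. A constant school effect is a strong assumption that the sample size section never states. The analysis section does not say whether the differences at T2 and T3 are adjusted for baseline, and it names no averaged contrast. Condensing a protocol explains a short list, but not a conclusion that the printed list does not support.

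**Conclusion.** The concern holds in this form: the stated 80% power does not follow from the listed parameters. Without repeated-measures gain, 24 schools of 50 give about 41-44% power at 0.20 and detect about 0.31-0.33 with 80% power; 80% at 0.20 would take about 58-60 schools. The article establishes neither 41-44% nor 80% as the power of the planned analysis, because the deciding correlation is missing.

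The arithmetic is secure under its assumptions (standardised effect, two-sided test, school-level ICC, equal school sizes). The article names neither the effect metric nor the sidedness of the test. A one-sided test would not rescue the figure, since it gives 54-56%.

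**What to change.** Keep the 24 schools and correct the statement, according to what was actually assumed.

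- **If no repeated-measures gain was assumed:** restate the power as about 41-44% at 0.20 and the effect detectable with 80% power as about 0.31-0.33.
- **If a gain was assumed:** restore item 3 by giving the child-level and school-level correlations over time and the formula. Make the primary contrast at T2/T3 explicitly baseline-adjusted so that it matches the calculation, and say whether it is one time point or an average. Give power over a range of correlations and ICCs.

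In either case, name the effect metric and say whether the test is two-sided.

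The cost is a change of wording and, in the second case, a short table. No extra schools are required. The stated power may become less favourable.

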**Methods:**

This study will conduct a cluster randomized controlled trial (RCT) in a large sample of Chinese rural children. Four rural counties in Shandong (Central China), Henan (Central China), Inner Mongolia (Northern China), and Xinjiang (Western China) will be selected as study settings from which schools will be sampled. Each sampled school will be randomly allocated either the intervention groups or a control group. Randomization will be performed by the research member who is not involved in the intervention stage. In each school students in grade 5 or higher will be recruited to ensure that approximately 50 children aged 10 to 18 years will be included. In each county, one high school, one middle school, and one primary school will be randomly chosen as the intervention group, and the other three similar schools will be chosen as control (waiting list) groups. A standardized and uniform research protocol will be applied in all intervention schools. All school social workers and psychological teachers would receive one week of in-person training following procedures. School-based psychosocial interventions included 14 group sessions for 14 consecutive weeks.

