### Statistical methods

All analyses are on an intention-to-treat basis, with all randomized participants included in the analysis and analyzed according to original group assignment regardless of treatment dose received. Descriptive statistics will be used to summarize the characteristics of the participants. Generalized linear mixed models (GLMMs) will be used to evaluate the effectiveness of the intervention on outcomes using a three-level multilevel model. This model includes intervention status, time, and the treatment between intervention and time as fixed effects. Dependency in the repeated measurements within individuals will be modeled using a random intercept and random slope at the participant level. A random intercept at the school level will be used to model dependencies between children within the same school. The interaction between treatment and schools will also be tested to investigate the cluster effects. Confounders will also be included as fixed effects in the model, including gender, age, parent characteristics, and teacher characteristics. The estimated intervention effect will be reported as the mean outcome differences (at T2, T3) and 95% confidence interval (95% CI) between the intervention and control groups. All covariate-by-condition interactions on child mental health will be examined.

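### An exclusion tied to completing the programme, with children described as recruited after schools are allocated, risks selecting children differently in the two arms

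*Protocol article*

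**What the plan says.** All references are to the protocol article.

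- *Exclusion* (Sample sizes and subjects): "Children with severe physical and mental health problem, and unable to participate into the program completely".
- *Inclusion* (same section): "all children in the program schools who have signed informed consent will participate in this program".
- *Unit of randomisation* (Study design and randomization): "School as the study unit will be randomly assigned to the intervention or the control group".
- *Allocation, then recruitment* (same section): "The schools were randomly allocated to either the intervention or control group using a random number generator"; two sentences later, "Grade 5 above in each school will be recruited to ensure that approximately 50 children aged 10 to 18 years are included". The abstract uses the same order: "Each sampled school will be randomly allocated either the intervention groups or a control group", with the recruitment of students described afterwards.
- *Independence*: the person who randomises is not involved in the intervention stage. Nothing similar is said of those who recruit children or judge eligibility.
- *Control condition* (Interventions): waiting-list schools give usual care throughout follow-up.
- *Calendar* (Project activities): baseline data are collected in the second half of 2023 and the intervention runs in 2024. Randomisation is not dated.
- *Analysis set* (Statistical methods): intention-to-treat, "with all randomized participants included in the analysis and analyzed according to original group assignment regardless of treatment dose received".

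**The concern.** Whether a child can take part fully in the programme is a concrete question in a school about to run 14 group sessions. In a school that will run none during follow-up, it has no clear meaning. If the judgement is made once a school's arm is known, the criterion may remove children in intervention schools and few or none in waiting-list schools.

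Randomising schools makes the schools comparable. It does not make the enrolled children comparable if they enter after allocation under a rule that works differently by arm. Children with a severe problem who cannot take part would plausibly score higher (worse) on the PCL-5, the primary outcome. Removing them from one arm lowers that arm's mean and looks like benefit. The planned effect is only 0.20 SD, so a modest imbalance matters.

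**Working it through.** **1. Does the criterion depend on the arm?** The exclusion joins two conditions with the word *and*. Read together, they exclude only children who have a severe problem and also cannot take part. Read separately, they exclude either group. On both readings the second condition refers to the programme. The school-level criterion in the same paragraph uses that word for a psychosocial intervention, and the Interventions section gives the intervention to one arm only during follow-up. The condition is therefore defined for one arm and unclear for the other.

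**2. What order is described?** The abstract and the Study design and randomization section both give allocation first and recruitment second. The latter puts allocation in the past tense and recruitment in the future tense. No section dates one against the other, and the flowchart is not available here. The order is implied, not stated.

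**3. How large could the effect be?** The article gives no figure for exclusions, so this is a sensitivity calculation on assumed values.

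Inputs from the article: planned effect 0.20; intraclass correlation 0.05; 24 schools of 50 children (24 × 50 = 1200), 12 schools per arm at 1:1; 5% significance, taken as two-sided.

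Assumed: *q*, the share excluded in intervention schools only; *d*, the amount in SD by which excluded children score worse than those retained; no adjustment for T1.

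If *R* is the mean of retained children, the full arm mean is (1 − q)R + q(R + d) = R + qd. Exclusion therefore lowers the arm mean by q × d.

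For the error rate, ignoring attrition:

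- design effect = 1 + (50 − 1) × 0.05 = 3.45
- effective children per arm = 12 × 50 / 3.45 = 173.9
- standard error of the difference = √(2 / 173.9) = 0.107 SD
- two-sided error under no true effect = Φ(b/0.107 − 1.96) + Φ(−b/0.107 − 1.96), with b = qd

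| q | d (SD) | Shift qd (SD) | Share of 0.20 | Nominal 5% error becomes |
|---|---|---|---|---|
| 2% | 0.5 | 0.010 | 5% | 5.1% |
| 5% | 0.5 | 0.025 | 12.5% | 5.6% |
| 5% | 1.0 | 0.050 | 25% | 7.5% |
| 10% | 0.5 | 0.050 | 25% | 7.5% |
| 10% | 1.0 | 0.100 | 50% | 15% |

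If *d* is measured from the whole-arm mean instead, the shift is qd/(1 − q). For d = 1 this gives 0.05/0.95 = 0.053 and 0.10/0.90 = 0.111, so the choice hardly matters.

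**4. What could the analysis remove?** PCL-5 is measured at T1 and the model contains an intervention-by-time term. If selection shifts T1 and T2 by the same amount, the change contrast is qd − qd = 0. If excluded children would also have changed differently over time, that part remains. The effect is to be reported as mean differences at T2 and T3, and the listed confounders (gender, age, parent and teacher characteristics) do not include baseline PCL-5. The article therefore does not settle how much would be absorbed.

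**The case against.** The strongest reply is that this is loose wording in a condensed article. The programme may mean the whole study, in which case the criterion applies equally in both arms. Sentence order is not a timeline, and tense is a poor guide here: the same section says schools will be assigned and were allocated, and the Interventions section describes a future intervention partly in the past tense. The sampling rule and recruiter blinding are details that an article may leave to the full protocol. Much of this stands. The order is an inference, and the absence of those details is not itself the finding. What remains is a criterion in the current text whose plain wording depends on the arm, beside two descriptions that both place allocation first.

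A reader might infer three stronger points that the article does not support:

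- *That the exclusion contradicts intention-to-treat.* An exclusion applied before enrolment is compatible with analysing every enrolled child as assigned, whatever dose was received. The criterion speaks of children unable to participate, not of children who failed to complete. A conflict would arise only if it were used during or after the programme to drop enrolled children, and no section says so.
- *That staff who know the allocation choose the 50.* Nothing says who selects children or what they know. Taking all consenting children and aiming for about 50 per school can coexist, for example by recruiting whole classes.
- *That no model could repair the bias.* T1 and the intervention-by-time term may absorb part of an imbalance already visible at baseline.

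**Conclusion.** The concern holds as a risk of differential selection. The exclusion is tied to a programme that one arm does not receive during follow-up, and school allocation is described before children are recruited. The article does not show that such selection will occur.

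On assumed values of 5% to 10% excluded in intervention schools only, scoring 0.5 to 1 SD worse than those retained, the unadjusted shift is 0.025 to 0.10 SD against a planned effect of 0.20. At 2% and 0.5 SD it is 0.01 SD and negligible. These figures assume no matching exclusions in waiting-list schools and no use of T1; either would reduce them. The direction, towards apparent benefit, rests on the assumption that excluded children have worse scores.

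The point should be corrected because the remedy is cheap and a selection imbalance is hard to undo with confidence afterwards.

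**What to change.** 1. Replace the programme-dependent wording with an eligibility criterion assessed at baseline and applied identically in all 24 schools. Make clear whether its conditions must hold together or are separate grounds.
2. Select the roughly 50 children per school by one rule in both arms: a random draw from grade lists, or whole classes.
3. Complete eligibility, consent and T1 in each school before its allocation is disclosed, and state this order.
4. State that no enrolled child is removed for incomplete participation.

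The cost is protocol wording and the order of field steps. Schools learn their allocation later, and the staff training listed among the intervention modules has to follow disclosure because it reveals the arm. Baseline work in the second half of 2023 and an intervention in 2024 leave room for this.

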### Interventions

A standardized and uniform research protocol was applied in all intervention schools. Schools in the intervention group will participate in all intervention modules listed in Table 1. All school social workers and psychological teachers would receive one week of in-person training following procedures. School-based psychosocial interventions included 14 group sessions for 16 consecutive weeks. Child groups and guardian groups met concurrently, with joint child guardian activities in some sessions. Child group sessions were led by 1 social worker and 1 headteacher, and guardian group sessions were led by 1 social worker, with social workers randomly assigned to groups to allow examination of social worker-level effects. Schools randomized to the waiting-list control group will provide usual care throughout the follow-up time, including services to which children had access that could affect mental health.

**Table 1 Tab1:** Intervention modules

Objectives	Content	Subjects	Duration	Stage
**Trauma-focused Cognitive Behavioral Intervention Unit**	Provides a supportive environment to help identify child trauma and mental health problem	Psychology teachers; social workers	One week	Beginning of semester
		Head teachers	Three days	
		Administrative staff	One day	
**Recognize common mental health problems**	Help parents and students understand common mental health problems, help parents identify children’s mental health problem	Children/Parents	2 sessions	Beginning of semester
**Cognitive processing of the trauma**	Help students and parents recognize the trauma and its’ characteristics	Children/Parents	2 sessions	2st week at semester
**Affective regulation management, relaxation**	Stress coping skills, resilience, empowerment	Children	3 sessions,	4th week at semester
**Trauma narrative, in vivo mastery of trauma reminders**	Emotional expression and cognition training	Children/Parents	2 sessions	6th week at semester
**Psychoeducation and parenting skills**	Effective parent‒child communication and response during traumatic events	Children/Parents	2 sessions	8th week at semester
**Conjoint child–parent sessions**	Sharing the trauma narrative	Children/Parents	1 session	10th week at semester
**Enhancing future safety and development**	Making a safety plan	Children/Parents	1 session	12th week at semester
**Program evaluation**	Satisfaction evaluation	Children/Parents	1 session	16th week at semester

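### Social workers are randomised to groups so that their effects can be examined, but the model has no social-worker, group or school-by-time term, so post-baseline clustering in the intervention arm is only partly captured

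*Protocol article*

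**What the plan says.** On delivery, the protocol article (Interventions) says: "Child group sessions were led by 1 social worker and 1 headteacher". Guardian groups have one social worker. Social workers are allocated to groups at random, "with social workers randomly assigned to groups to allow examination of social worker-level effects". The number and size of groups per school are not given.

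On analysis, Statistical methods sets out a mixed model, "using a three-level multilevel model". Its parts are:

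- Fixed effects: "This model includes intervention status, time, and the treatment between intervention and time as fixed effects".
- Participant level: "Dependency in the repeated measurements within individuals will be modeled using a random intercept and random slope at the participant level".
- School level: "A random intercept at the school level will be used to model dependencies between children within the same school".
- Cluster check: "The interaction between treatment and schools will also be tested to investigate the cluster effects".
- Covariates: "Confounders will also be included as fixed effects in the model, including gender, age, parent characteristics, and teacher characteristics".

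The effect is to be reported as mean differences between arms at T2 and T3 with 95% confidence intervals. In Aims and hypotheses, the effectiveness hypotheses are worded as a decrease in the intervention schools that is not seen in the control schools.

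**The concern.** Two things do not fit together.

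First, a design feature is given a purpose that the stated model does not serve. The three levels are measurement, child and school, which leaves no level for group or social worker.

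Second, children who share a group and its leaders will tend to respond alike. That similarity starts after baseline and exists only in the intervention arm. A school intercept that is the same at T1, T2 and T3 and in both arms has the wrong shape for it. If the shared variation is left out of a standard error, the confidence interval is too narrow and the test rejects too often under the null.

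**Working it through.** **Which terms could carry a shared post-baseline effect**

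- School random intercept: constant over time, so it drops out of any change from T1.
- Participant intercept and slope: independent between children, so they cannot represent an effect shared by a group.
- Treatment-by-school interaction: each school is in one arm, so it cannot be separated from the school effect.
- Teacher characteristics: fixed covariates, not a shared group or worker effect.

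**Inputs**

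The article gives no figure on this point to reproduce. From Sample sizes and subjects: 24 schools allocated 1:1, so 12 per arm; 50 children per school with 20% attrition, so 50 × 0.80 = 40; intraclass correlation 0.05; 5% significance, taken as two-sided.

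Assumed, because the article does not state them: total variance 1 before any group effect; within-child correlation r = 0.6 in the non-school variance of 0.95; k = 1, 2 or 4 groups per school; post-baseline group variance g = 0.02 or 0.05.

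**Arm-by-time contrast (change from T1 to T2)**

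Variance the model allows for, with 480 children per arm (12 × 40):
2 × [2 × 0.95 × (1 − 0.6)] / 480 = 1.52 / 480 = 0.00317.

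Variance added by groups in one arm: g / (12k).

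Ratio R = (0.00317 + g/(12k)) / 0.00317. Type I error = 2 × [1 − Φ(1.96/√R)].

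| g | k | added variance | R | type I error |
|---|---|---|---|---|
| 0.02 | 1 | 0.00167 | 1.53 | 11.3% |
| 0.02 | 2 | 0.00083 | 1.26 | 8.1% |
| 0.02 | 4 | 0.00042 | 1.13 | 6.5% |
| 0.05 | 1 | 0.00417 | 2.32 | 19.8% |
| 0.05 | 2 | 0.00208 | 1.66 | 12.8% |
| 0.05 | 4 | 0.00104 | 1.33 | 8.9% |

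Simulation at g = 0.05 (6,000 runs per cell) gave 19.3%, 12.6% and 8.3% for k = 1, 2 and 4. REML fits that included the participant slope (1,500 null runs per cell) gave 18.9%, 12.1% and 8.8%, against 5.7% with no group effect, so the slope does not protect the test.

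**Between-arm mean difference at T2**

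Here the school variance stays in the standard error. With no group effect the variance is (2/12) × (0.05 + 0.95/40) = 0.01229.

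Take the worst case, k = 1 and g = 0.05. The true variance is 0.01229 + 0.05/12 = 0.01646. The fitted school variance also rises. A shared effect present at two of three times contributes (2/3)² = 4/9 of g to the variance of the school's average over time. It does so in half the schools, hence about (2/9) × 0.05 = 0.0111. The model variance becomes about (2/12) × (0.0611 + 0.95/40) = 0.01414.

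The ratio is 0.01646 / 0.01414 = 1.16. With t on 22 degrees of freedom (critical value 2.074), 2.074/√1.16 = 1.92, a type I error of about 6.8%.

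Simulation (3,000 runs per cell, t on 22 degrees of freedom) agrees. For k = 1, 2 and 4 it gave 5.5%, 5.5% and 5.2% at g = 0.02, and 6.9%, 4.9% and 5.9% at g = 0.05.

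**Allowing for clustering after baseline**

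An analysis of school means, which lets schools vary in their change over time, gave 4.6% to 5.4% in the same settings.

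**The case against.** The strongest reply is that the larger figures belong to a contrast the article does not say it will report. Statistical methods promises mean differences at T2 and T3. For these the school intercept enters the standard error and absorbs much of the clustering. This stands, and it limits the size of the point. A reader might infer that intervention-arm clustering is ignored altogether; the school intercept shows that it is not. The arm-by-time test still matters, because the hypotheses concern change and the interaction is in the model.

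A second reply is that random assignment only makes the examination possible and does not promise a term in the main model. This also stands in part. A reader might infer that social-worker effects cannot be studied in this trial. That is true only of the model as written: random assignment keeps the question open if group membership is recorded and the layout separates workers from schools.

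A third reply is that a condensed article may leave facilitator analyses to an analysis plan that is not shown. That would excuse silence. Here, however, the article states the levels and random effects of its model, and those have the wrong shape for the clustering that its own delivery creates.

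Finally, the number of groups, the group variance and the within-child correlation are all assumed. The 20% figure needs one group per school, and in that case worker and school are confounded unless workers cross schools.

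**Conclusion.** The point holds in a limited form. The model has no term for the social-worker effects that the random assignment is meant to reveal, and its school intercept captures only part of the post-baseline clustering in the intervention arm.

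Under the stated assumptions, the arm-by-time test has a type I error of about 7% to 11% at group variance 0.02 and 9% to 20% at 0.05. The between-arm difference at T2 or T3 has about 5% to 7%. The documents do not support quoting the upper figures as the error rate of the reported effect. Which range applies depends on which contrast is tested, and the article leaves room for either.

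**What to change.** Add a school-by-time random term to the main model, so that both the arm-by-time test and the T2 and T3 differences carry clustering that arises after baseline.

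Record group and social-worker identifiers for every child in the intervention arm. Where a school has more than one group, or workers cross schools, fit a worker (or group) random effect that acts only in the intervention arm at T2 and T3. Report its variance as the planned examination of worker effects. If that variance is estimated at zero or the model does not converge, keep the school-by-time term for the main effect. With one worker per school, state that worker and school effects cannot be separated.

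The cost is some analysis wording, two identifier fields, one or two imprecisely estimated variance parameters and slightly wider confidence intervals. The identifiers matter most: without them the worker question is lost whatever model is chosen.
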